**Smart mental health Visit schedule and analysis for visit:**

The study will be reported in mainly 2 category:-

1. Baseline (As applicable, this will includes ASHA screening data available in in ASHA Screening 1 and ASHA follow up 1. OR Baseline data collected by study interviewers)
2. Post Intervention (collected by study interviewers)

All the subject at post intervention are screen positive subjects. They were screened positive either at Baseline by study interviewers or at Intervention visits (ASHA screening 1 and ASHA follow-up 1) by ASHA. All the screen positive subjects were followed by ASHAs which is available in the ASHA follow up data.

Unless otherwise stated, the summary tables will be presented under 2 category:-

1. Baseline
2. Post Intervention

The difference between Baseline and Post Intervention will provide effect of intervention.

Apart from the Post Intervention data, post stigma data was also collected. At the time of creating derived data for post Intervention, both data (Post Intervention and post stigma) are appended together and created a single data set. A flag variable containing record ("Post Intervention" & "post stigma") was created was created in derived data set to identify such records.

Unless otherwise stated, all the analysis will be presented for all the subject who are screen positive by ASHA.

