#### **Case control Analysis of Primary objective:**

All the subjects screened positive by ASHA are case here. The subjects who mental health are screen negative by ASHA, but screen positive by interviewer are kind of control in this study setup. Such subjects will be called as control.

A case control analysis will be performed to assess the difference in anxiety and depression score and mental health service utilization.

For this difference in anxiety and depression score for individual subjects will be computed from ASHA screen data and post intervention data. Further this difference in case and control will be statistically analyses by 2 independent sample t-test. Difference of difference in score between case and control along with p-value will be presented.

For health service utilization between cases and control, Count along with percent and Chi- square P-value will be presented.

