**Proportion of subject used health services**

| Category | Baseline | Post Intervention | P-Value |
|-----------------|-----------------|--------------------------|----------------|
| Case*           | xxxx            | xxxx                     | 0.xxx          |
| Control**       | xxxx            | xxxx                     |                |

*Health Service used: At baseline: Response from the question “Did you get treated for that mental disorder?”*

*At Post Intervention: Response from the question “Did you get treated for your mental health condition as indicated by ASHA/Interviewer?”*

*\* Case: The subjects who are screen positive by ASHA.*

*\*\* Control: The subjects who are screened negative by ASHA but positive by study interviewer.*

*P-Value is calculated based chi-square independent sample test of proportion.*

Table 17: Subject Referrals during ASHA screening

| Screened by |                                                                                                            | (N*=xxxxxx)
n(%) |
|-------------|------------------------------------------------------------------------------------------------------------|---------------------|
| ASHA        | Out of those Screened by ASHA Proportion of subject referred to the PHC doctor                             | xxxx (xx.xx)        |
|             | Out of those referred to PHC doctors Proportion of subjects actually visited doctors                       | xxxx (xx.xx)        |
|             | Out of those visited doctors Proportion of subjects appropriately prescribed anti-depressant or anxiolytic | xxxx (xx.xx)        |
|             | Out of those visited doctors Proportion of subjects appropriately referred by the PHC doctor for more      | xxxx (xx.xx)        |

\*N= overall population screened by ASHAs.

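### The SAP's own text places the case-control 'controls' among subjects followed by ASHAs, so Tables 16a and 16b cannot be read as intervention versus no intervention

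*SAP*

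**What the plan says.** The SAP section on the visit schedule describes the subjects seen after the intervention, all of them screen positive: "They were screened positive either at Baseline by study interviewers or at Intervention visits (ASHA screening 1 and ASHA follow-up 1) by ASHA". It continues: "All the screen positive subjects were followed by ASHAs which is available in the ASHA follow up data". The same section locates the intervention effect in the before-after comparison: "The difference between Baseline and Post Intervention will provide effect of intervention".

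The section 'Case control Analysis of Primary objective' then forms two groups. Cases: "All the subjects screened positive by ASHA are case here". Controls: "The subjects who mental health are screen negative by ASHA, but screen positive by interviewer are kind of control in this study setup". The purpose is stated as: "A case control analysis will be performed to assess the difference in anxiety and depression score and mental health service utilization". Score changes are compared by a two-sample t-test, with the difference in change and its p-value reported (Table 16a). Service use is compared by chi-square (Table 16b).

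Table 15 has a separate block for interviewer-positive subjects, footnoted as those not positive by ASHA. It gives them their own baseline versus post-intervention p-value.

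**The concern.** A control group is informative about an intervention only if its members did not receive that intervention, or received a known and smaller amount of it. Here the same people appear to be used in two ways. In the visit-schedule section they are among the followed subjects, and in Table 15 they contribute a before-after difference of the kind the SAP calls the effect. In Tables 16a and 16b they are the comparator.

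The contrast sits under a heading naming the primary objective, uses the word 'control' and ends in a p-value for the difference in change. A reader will naturally take it as a controlled estimate. If controls were also exposed, a small or non-significant difference would say little about whether the intervention worked. If they were not exposed, the visit-schedule section misstates who was followed. One of the two sections needs correcting in either case.

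**Working it through.** The SAP states no sample size, power, significance level or effect size, and its tables are empty shells. There is no figure to reproduce, so the main check is of the text.

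**Who the controls are**

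1. Screen positives at post intervention are a union: interviewer-positive at baseline, or ASHA-positive at ASHA screening 1 or ASHA follow-up 1 (visit-schedule section).
2. Every member of that union is said to have been followed by ASHAs (next sentence of that section).
3. Controls are ASHA-negative and interviewer-positive (case-control section), so they fall inside the union through its first branch.
4. From 1 to 3, controls were followed by ASHAs.
5. Could 'screen positive' in step 2 mean ASHA-positive only? The wording is against it. When the section means the narrower group, in its last sentence, it adds that the positives are those found by ASHA.
6. Is there an exemption elsewhere? None was found. The case-control section calls these subjects only a kind of control and does not say what they did or did not receive.

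**What 'followed' covers**

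7. The term is not defined. 'ASHA follow-up 1' is also a source of screening and baseline data (visit-schedule and data-selection sections), so some follow-up may be no more than re-screening.
8. Referral to the PHC doctor is described only for subjects on the ASHA pathway (section on referral; Table 17).

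Steps 1 to 6 establish that the text puts controls in the followed group. Steps 7 and 8 show that the degree of exposure is left open.

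**Illustration of the consequence (assumed inputs, not from the SAP)**

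Let d be the effect in SD units and f the share of it that controls also receive. If the groups are otherwise comparable, the contrast is d × (1 − f). With n per group and two-sided 5%, power ≈ Φ(d(1 − f)√(n/2) − 1.96). Choosing n for 80% power at f = 0 gives 63 per group for d = 0.5 and 175 per group for d = 0.3. Both give d√(n/2) = 2.806, hence the same power:

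| f | contrast, d = 0.5 | contrast, d = 0.3 | power |
|---|---|---|---|
| 0 | 0.500 | 0.300 | 0.80 |
| 0.25 | 0.375 | 0.225 | 0.56 |
| 0.50 | 0.250 | 0.150 | 0.29 |
| 0.75 | 0.125 | 0.075 | 0.10 |
| 1 | 0 | 0 | 0.025 (one tail of the type I error) |

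For example, at f = 0.5 the power is Φ(1.403 − 1.96) = Φ(−0.557) = 0.29.

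**The case against.** The strongest reply is that being followed is not the same as receiving the intervention. The SAP never equates them, part of the follow-up data serves as screening, and referral is documented only for the ASHA pathway. What the intervention comprised is normally left to the protocol, which is not shown. This stands. A reader might infer that the contrast compares two equally exposed groups and can show nothing of the effect. The document does not support that: it gives no degree of exposure, and the contrast vanishes only at f = 1. Below that it is diluted.

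A second reply is that the SAP does not claim the contrast measures the intervention effect. It assigns the effect to the before-after difference and hedges the word 'control'. This also stands as far as it goes. But the placement under the primary objective and the p-value for the difference in change invite an effect reading, and no caveat warns against it.

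A third concerns the post-intervention item in Tables 15 and 16b: "Did you get treated for your mental health condition as indicated by ASHA/Interviewer". A reader might infer from it that controls had been told of their condition. The item is generic and also appears in Table 14b, which is limited to ASHA-positive patients. It does not show that any control was told anything, and the point does not rest on it.

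Finally, the (1 − f) formula assumes groups that differ only in exposure. These groups are defined by the ASHA screening result, so they differ by selection as well. The formula shows how shared exposure acts and does not predict the result of Tables 16a and 16b.

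**Conclusion.** The point holds in a limited form. Read as written, the SAP includes the controls among the subjects followed by ASHAs, and it nowhere states that they were unexposed. The contrast in Tables 16a and 16b therefore has no basis as a comparison of intervention with no intervention. Any shared exposure dilutes it by an amount that cannot be derived from the document; the power figures above rest wholly on assumed inputs.

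The conclusion assumes that 'screen positive' keeps the same meaning across two adjacent sentences of the visit-schedule section. If the sponsor meant ASHA-positive subjects only, the controls may indeed be unexposed, but then that section is wrong and must be corrected. The correction should be made because it changes what the p-value for the difference in change can be taken to show. This point does not bear on the separate before-after analyses of ASHA-positive subjects.

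**What to change.** 1. Reconcile the visit-schedule section with the case-control section: state whether ASHA-negative, interviewer-positive subjects were followed by ASHAs, and what that follow-up comprised.
2. From the ASHA follow-up and doctors' follow-up data, which the SAP indicates are held, tabulate for cases and controls the share with any ASHA follow-up and the share with a doctor visit. Separate re-screening at ASHA follow-up 1 from later follow-up.
3. Unless the controls prove essentially unexposed, drop the 'control' label and any effect reading. Present Tables 16a and 16b as a descriptive comparison of ASHA-detected and ASHA-missed subjects.
4. Do not redefine controls as those without a follow-up record. That selects on an event after baseline (such subjects may be absent, unwilling or not linked), and cases would not be restricted in the same way.

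The cost is a small amount of extra tabulation, with no new data collection, and a weaker claim from Tables 16a and 16b.

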**Data selection criteria for Analysis:**

Unless otherwise stated, for baseline we have to use ASHA screening (ASHA screening 1 and ASHA follow-up 1) data. At post intervention we have to use Post intervention data collected by study interviewers linked with patient ID of ASHA screen positive data.

For certain tables the information at baseline may not be collected by ASHA during their screening. For all such instance, Baseline data collected by study interviewers will be used linked with patient ID of ASHA screen positive data.

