#### **Secondary Analysis Depression and Anxiety Score:**

The subjects are classified as screen positive if he/she fulfil either one of below mentioned three category:-

1. Depression Sore  $\geq 10$
2. Anxiety Score  $\geq 10$
3. Suicidal tendency Score  $\geq 1$

The depression and anxiety will be categorized as Normal if their total score is in between 0-

4. The score in between 5-9 will be classify as Mild. The score in between 10-14 will be classify as moderated. The score of 15 or greater will be treated as severe.

The Anxiety and Depression score will be categorized by their severity. The count and percentage for depression and Anxiety at baseline and post baseline will be presented by severity. A separate table will be presented for depression score  $\geq 10$  and anxiety score  $\geq 10$  at baseline and post intervention.

A separated table will be provides for the only screen positive subjects with the count and percentage of the symptoms which lead them to be screen positive.

The summary statistics (N, Mean, STD, Min and Max) for anxiety and depression score by visit will be presented. The difference in score between baseline and post intervention will be summarized in similar fashion. The mean difference in score between baseline and post intervention will be statistically analyzed by paired t-test. The p-value from the analysis will be presented in same table.

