|             | Difference        | xxxxx             | xx.xx (x.xxx) | xx.xx  | xx.x, xx.x | 0.xxx   | xxxxx                | xx.xx (x.xxx) | xx.xx  | xx.x, xx.x | 0.xxx   |

Table 8b: Change in Depression/Anxiety Score from Baseline to Post Intervention for those who had a score  $\geq 10$  at the beginning of the intervention as screened by ASHAs

| Visit             | -----Anxiety----- |               |        |            |         | -----Depression----- |               |        |            |         |
|-------------------|-------------------|---------------|--------|------------|---------|----------------------|---------------|--------|------------|---------|
|                   | N                 | Mean (SD)     | Midian | Min, Max   | P-value | N                    | Mean (SD)     | Midian | Min, Max   | P-value |
| Baseline          | xxxxx             | xx.xx (x.xxx) | xx.xx  | xx.x, xx.x |         | xxxxx                | xx.xx (x.xxx) | xx.xx  | xx.x, xx.x |         |
| Post Intervention | xxxxx             | xx.xx (x.xxx) | xx.xx  | xx.x, xx.x |         | xxxxx                | xx.xx (x.xxx) | xx.xx  | xx.x, xx.x |         |
| Difference        | xxxxx             | xx.xx (x.xxx) | xx.xx  | xx.x, xx.x | 0.xxxx  | xxxxx                | xx.xx (x.xxx) | xx.xx  | xx.x, xx.x | 0.xxxx  |

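### The score change called the effect of intervention starts from the ASHA screen that selected the subjects and ends with a different rater, so regression to the mean counts as benefit and any rater difference is mixed in

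*SAP*

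**What the plan says.** The section on visit schedule and analysis equates change with effect: "The difference between Baseline and Post Intervention will provide effect of intervention". It also sets the default population: "Unless otherwise stated, all the analysis will be presented for all the subject who are screen positive by ASHA". On how subjects became positive it says: "They were screened positive either at Baseline by study interviewers or at Intervention visits (ASHA screening 1 and ASHA follow-up 1) by ASHA".

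The section on data selection criteria makes the same ASHA visits the default baseline: "Unless otherwise stated, for baseline we have to use ASHA screening (ASHA screening 1 and ASHA follow-up 1) data". The other end of the comparison has a different source: "At post intervention we have to use Post intervention data collected by study interviewers linked with patient ID of ASHA screen positive data". Interviewer baseline data, linked by patient ID, are the fallback for items that ASHAs did not collect.

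The secondary analysis section defines screen positive as depression score of at least 10, anxiety score of at least 10, or suicide score of at least 1. Two of the three entry rules are therefore the outcome scores themselves. The test is: "The mean difference in score between baseline and post intervention will be statistically analyzed by paired t-test". Table 8b repeats it in subjects with a score of at least 10 "at the beginning of the intervention as screened by ASHAs". Tables 7a and 8a also carry separate Interviewer rows; in Table 8a these include a difference and its own p-value.

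**The concern.** When a subject enters the table because a measurement was high, and that measurement is also the starting point for change, part of the starting value is chance error that will not recur. The mean falls at the next measurement with no intervention at all. An unadjusted paired t-test cannot separate this from benefit.

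The change of rater is a second, separate problem. If interviewers score systematically differently from ASHAs, that difference enters the change in full. Nothing in the SAP deals with regression to the mean, rater agreement or calibration.

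The primary objective names the anxiety and depression scores. If the change is read as the SAP says it should be, a significant result for those scores could not tell an intervention that works from one that does nothing.

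**Working it through.** The SAP states no mean, SD, correlation, sample size or expected effect, so there is no figure of its own to reproduce. The only numerical input from the document is the threshold of 10. Everything else below is assumed: population mean 4, SD 5, correlation ρ between the ASHA score and the later interviewer score of 0.5, 0.65 or 0.8, zero true effect, and a two-sided 5% test.

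**1. False fall when the score itself is selected at 10 or more (Table 8b), normal model.**

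- z = (10 - 4)/5 = 1.2; φ(1.2) = 0.1942; 1 - Φ(1.2) = 0.1151; ratio λ = 1.688.
- Excess of the selected mean over the population mean: 5 × 1.688 = 8.44, so the selected baseline mean is 12.44.
- Expected fall = (1 - ρ) × 8.44.
- Baseline variance after selection: V = 25 × (1 + 1.2 × 1.688 - 1.688²) = 4.43.
- SD of change = √[(1 - ρ)² × 4.43 + 25 × (1 - ρ²)].
- Paired t at n=100 = -10 × fall / SD.

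| ρ | Fall | SD of change | t at n=100 | Fall, integer scores | t, integer scores |
|---|---|---|---|---|---|
| 0.5 | 4.22 | 4.46 | -9.5 | 4.0 | -9.2 |
| 0.65 | 2.95 | 3.87 | -7.6 | 2.8 | -7.3 |
| 0.8 | 1.69 | 3.03 | -5.6 | 1.6 | -5.4 |

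The last two columns are a simulation of 2,000,000 subjects with scores rounded and limited to an assumed range of 0 to 27. With the mean varied over 3 to 5 and the SD over 4 to 5, the normal-model fall runs from 1.4 to 4.6 points. The probability of a significant result is then at least 0.94 at n=50 and above 0.99 at n=100.

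**2. Rater shift.** If interviewers score 1 point lower than ASHAs, the simulated falls become 4.9, 3.8 and 2.6 points. If they score 1 point higher, the falls become 3.0, 1.8 and 0.6. In the mildest case (ρ = 0.8, shift +1), t at n=100 is still about -2.1.

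**3. Dilution in Table 8a.** Here subjects can enter on the other scale or on the suicide score. With an assumed depression-anxiety correlation of 0.5 to 0.7, 0 to 10% of subjects positive on the suicide item independently of the scores, and no rater shift, the false fall is 0.7 to 3.0 points.

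**4. Whether other planned analyses repair it.**

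- *Interviewer rows of Table 8a.* Rater type is constant, but the SAP does not say who is in these rows. If they are subjects whom the interviewer found positive, selection is again on the baseline, and the simulated false fall is the same 1.6 to 4.0 points without rater shift.
- *Case-control comparison.* Change is computed from ASHA scores. Controls are ASHA-negative, so their ASHA score is low by selection and drifts up by 1.4 to 1.7 points with no effect and no rater shift. The false case-minus-control difference is -3.1, -4.4 and -5.6 points at ρ = 0.8, 0.65 and 0.5, larger than the change in cases alone.

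**5. What the interviewer baseline achieves.** In the same ASHA-positive subjects, change from interviewer baseline to interviewer post is 0.0 points in every scenario above, because the ASHA score was assumed to correlate equally with both interviewer scores. In general the residual is (ρ with post - ρ with interviewer baseline) × 8.44. If the correlation with post is lower by 0.10, this is -0.84; by 0.15, -1.27; by 0.20, -1.69. Integer-score simulations give slightly smaller values (about -0.8, -1.1 to -1.2 and -1.5 to -1.6), against -2.8 to -4.0 from the ASHA baseline in the same settings.

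**The case against.** Several points on the other side stand, and they limit the claim.

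- A reader might infer that the rater change also counts as benefit. The SAP does not say that interviewers score lower than ASHAs; the shift could inflate benefit or hide it. Only regression to the mean has a known direction.
- A reader might infer that every subject was selected on a score of 10 or more. The entry rule also admits on the other scale or on the suicide item, so the Table 8b figures do not carry over to Table 8a.
- A reader might infer that no same-rater change is planned. The Interviewer rows of Table 8a are one. What is missing is a statement of their population, and hence whether they are free of selection on the baseline.
- A reader might infer that using two ASHA visits gives each subject two chances to cross the threshold. The SAP lists both visits as sources but does not say that screen-negative subjects were rescreened at the second.
- The paired t-test sits under the secondary analysis, and the score comparison under the primary objective is the case-control one. But the primary objective names the scores, the sentence on effect is general, and the case-control contrast does not remove the bias.
- All sizes rest on assumed inputs, and the t-values on an assumed n of 100.

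None of this touches the structure. The same ASHA screening selects the subjects and supplies their baseline, and the resulting difference is called the effect.

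**Conclusion.** The point holds and should be fixed before analysis. As written, the change in ASHA screen-positive subjects includes regression to the mean in the direction of benefit, plus any rater difference in an unknown direction. Under the assumptions shown, the false fall without rater shift is about 1.6 to 4.0 points in Table 8b, and a rater shift of 1 point moves it by about 1 point either way. Table 8a is affected less. A significant paired test would therefore be expected in Table 8b at moderate sample sizes even with no effect. This shows that the planned analysis cannot support the conclusion attached to it; it does not show that the intervention is ineffective.

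A reader might also infer that switching to the interviewer baseline gives an unbiased effect. It does not: the zero residual needs equal correlations, and natural remission and secular change remain in any uncontrolled before-after difference.

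**What to change.** 1. For the scores of ASHA screen-positive subjects in Tables 7b, 8a and 8b, take the baseline from the study-interviewer baseline linked by patient ID. Use the ASHA screen only to define who is in the table.
2. State the population of each row of Table 8a.
3. Keep the change from the ASHA baseline as a secondary row, labelled as affected by selection and rater change.
4. Report how many ASHA screen-positive subjects have no linked interviewer baseline.
5. Replace the sentence on effect in the visit schedule section with: *change from baseline; not by itself an estimate of intervention effect*.

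The cost is SAP wording and re-pointing one variable to data that the SAP already plans to link. The reported change is likely to be less favourable, and subjects without a linked interviewer baseline drop out of the main row; the SAP does not give their number.
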